### Primary outcome measure

The pain intensity after the surgical procedure will be evaluated using the VAS. The pain is related by the patient on a 100 mm horizontal visual analog scale. The two ends of the scale are 0 mm (no pain) and 100 mm (the most terrible pain that I can imagine). The patient will be asked to mark the scale based on their average pain during the evaluation period. The pain intensity will be evaluated before and after the surgical procedure. After surgery, pain will be evaluated on the first three postoperative days and at 1, 2, 3, 6, 12 and 24 months after the surgical procedure. Pain will also be evaluated according to Dennis’s scale at the 1, 2, 3, 6, 12 and 24 month follow-up visits.

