**Methods/designs:**

This study is designed as a multi-center, randomized controlled trial of patients aged 18–65 years who are scheduled to undergo surgical posterior fixation. Treatment by the conventional open approach or percutaneous minimally invasive approach will be randomly assigned. The primary outcome measure is postoperative pain, which will be measured using the visual analogue scale (VAS). The secondary outcome parameters are intraoperative bleeding, postoperative drainage, surgery time, length of hospital stay, SF-36, EQ-5D-5 l, HADS, pain medication, deambulation after surgery, intraoperative fluoroscopy time, vertebral segment kyphosis, fracture vertebral body height, compression of the vertebral canal, accuracy of the pedicle screws, and breakage or release of the implants. Patient will be followed up for 1, 2, 3, 6, 12 and 24 months postoperatively and evaluated according to the outcomes using clinical and radiological examinations, plain radiographs and computed tomografy (CT).

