### Statistical considerations

#### Sample size

Considering an expected reduction of two points in the visual analog pain scale (VAS) in 50% of the patients in group B compared to 25% those in group A after surgery with a significance level of 5% and a study power of 80%, and using the Z statistic, where p_1_ (0.5) and p_2_ (0.25) are previously defined, a minimum sample size of 58 patients was obtained, for each of the groups, according to the following formula:
$$ \mathrm{n}={\left( Z\alpha / 2+{Z}_{\beta}\right)}^2\ast \left({p}_1\left( 1-{p}_1\right)+{p}_2\left( 1-{p}_2\right)\right)/{\left({p}_1-{p}_2\right)}^2 $$

Where, Zα/2 is the critical value of the Normal distribution at α/2, i.e., 0.05 and critical value =1.96; Z_β_ is the critical value of the Normal distribution at β, i.e., 0.2 and critical value = 0.84; p_1_ and p_2_ are the previously defined sample proportions of the two groups.

Assuming an alpha of 0.5, a sample size of 58 patients per group was calculated to yield a power of 80% and detect a difference of one point between intervention groups in the 10-point VAS score. Standard differences were estimated to be 1.6 according to previous work (1) and drop-out rates were anticipated to be 28%”.

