### Primary outcome

In the analysis of the results regarding the outcomes, we will employ the relative risk (RR) and its 95% confidence interval (95% CI) and derived estimators, such as relative risk reduction (RRR), absolute risk reduction (ARR), risk difference (RD), number needed to treat (NNT), and number needed to damage (NND), emphasizing that in this clinical trial the intention-to-treat (ITT) principle will be used.. To verify the associations among the other variables, univariate analyses followed by multivariate analyses will be performed through logistic regression, also using RR and its 95% CI as association and magnitude estimators.

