### Secondary endpoints and safety profile

Considering the secondary outcomes (including minor and major adverse events [AE]), comparing the two groups (A versus B), and for comparing variables between groups A and B, when dealing with proportions, the chi-square test will be used, while for continuous variables the Student’s *t* test (if equal variances) will be used when dealing with averages or the Bonferroni e Benjamini-Hochberg test in the case of medians, in both cases, for independent samples. To minimize the interference of possible confounding variables (in both primary and secondary outcomes), all analyzes will be performed using necessary adjustments such as logistic regression, subgroup analyzes (age, sex, fracture type, duration of surgery, participant center, etc). A significance level of 5% shall be considered in all of the analyses described above.

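### The primary pain outcome has nine postoperative time points and two competing definitions, and none is named as primary, so the protocol fixes no single confirmatory test at 5%.

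*Protocol article*

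**What the plan says.** **Outcome.** The abstract and the opening of Methods/design name the primary endpoint only as postoperative pain on the VAS. Under *Primary outcome measure*, the scale is a 100 mm line and "pain will be evaluated on the first three postoperative days and at 1, 2, 3, 6, 12 and 24 months". A second pain scale, Dennis's, is added under the same heading at the six follow-up visits ("Pain will also be evaluated according to" that scale).

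**Sample size.** Two calculations each end at 58 per group:
- The first is on proportions: "Considering an expected reduction of two points in the visual analog pain scale (VAS) in 50% of the patients in group B", against 25% in group A. The timing is given only as after surgery.
- The second is on the score. The trial is to "detect a difference of one point between intervention groups in the 10-point VAS score", with 1.6 as the standard deviation and 28% anticipated drop-out.

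**Analysis.** Under *Primary outcome*: "we will employ the relative risk (RR) and its 95% confidence interval (95% CI) and derived estimators", followed by risk reductions and numbers needed to treat. The event that these count is not stated. Under *Secondary endpoints and safety profile*: "A significance level of 5% shall be considered in all of the analyses described above". Bonferroni and Benjamini-Hochberg are named in that same section, but as a test for comparing medians.

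**The concern.** A confirmatory trial needs one variable, one time point (or one summary over time) and one test to carry the type I error. Here the time point is open among nine, and the variable is open between a responder proportion and a score difference. Pain in the first days after surgery and pain at two years are different clinical questions, and the protocol treats them as one outcome.

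If the text is followed as written, nothing stops a favourable result at one of the nine assessments, on either definition, from being reported as the primary result. The significance level and power in the sample-size section would then not describe the claim actually made.

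This is more than detail left to an analysis plan. The protocol itself states two different primary variables and an error level for all analyses, so a later plan could settle the matter only by overriding part of it.

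**Working it through.** **1. Does the sample size show which definition is primary?**

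Inputs from *Sample size*: proportions 0.50 and 0.25; critical values 1.96 and 0.84; difference 1 point, SD 1.6; drop-out 28%.

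- *Proportions, pooled variance under the null* (mean proportion 0.375): n = [1.96·√(2·0.375·0.625) + 0.84·√(0.5·0.5 + 0.25·0.75)]² / 0.25² = 57.6, so **58**. This reproduces the stated figure.
- *Proportions, the unpooled formula as printed*: (1.96 + 0.84)² · 0.4375 / 0.0625 = 54.9, so 55.
- *Score difference*: 2 · (1.96 + 0.84)² · 1.6² / 1² = 40.1, so 41. With drop-out, 41 / 0.72 = 56.9, so **57**, within one patient of 58. This uses alpha 0.05. The 0.5 printed in that paragraph would give 12 per group, so it can be read as a misprint.

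Both definitions lead to about 58, so the sample size cannot tell the reader which one is primary.

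**2. Do the other sections settle it?**

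| Section | Points to |
|---|---|
| *Primary outcome measure* | a VAS score in mm at nine times |
| *Sample size*, first paragraph | a responder proportion, after surgery |
| *Sample size*, last paragraph | a one-point score difference, no time |
| *Primary outcome* | relative risk and derived measures, event undefined |
| *Statistical analysis* | generic tests by type of variable |

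The relative risk leans towards the responder version. The event, its threshold in mm and its time point are still not given there.

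**3. Error rate under an any-of-nine rule, one definition**

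Assumption: a two-sided 5% test at each of the nine times, with success claimed if any one is significant. The protocol does not state this rule and gives no correlation between times.

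Independent tests: 1 − 0.95⁹ = **37.0%**.

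With common correlation ρ between the nine normal test statistics, the risk is 1 − ∫ φ(u)·[Φ((1.96 − √ρ·u)/√(1−ρ)) − Φ((−1.96 − √ρ·u)/√(1−ρ))]⁹ du:

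| ρ (assumed) | Chance of at least one false positive |
|---|---|
| 0 | 37.0% |
| 0.3 | 32.6% |
| 0.5 | 26.9% |
| 0.7 | 20.2% |
| 0.8 | 16.5% |
| 0.9 | 12.4% |

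With correlation that decays with the order of visits (AR(1)), simulation gives 32.9% at 0.5, 27.5% at 0.7 and 17.4% at 0.9.

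**4. Both definitions allowed at all nine times**

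These are simulations with 25% responders under the null. The answer depends on how the two definitions are linked:
- Responder status as a cut of the same variable that the t test uses (58 per group): about 55% at ρ = 0, 43% at 0.5, 37% at 0.7 and 26% at 0.9.
- Responder status as change from baseline, t test on the postoperative score (42 or 58 per group): about 53% at 0.3, 50% at 0.5 and 46% at 0.7.

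Even at one fixed time point, allowing either definition gives about 8–9% in the first of these two models.

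**The case against.** The list of time points is a measurement schedule. It does not say that nine tests will be run or that any one of them would count as success. That is correct, so the 12–37% range is conditional. A reader might infer that the trial's false-positive risk simply is 20–37%. The documents do not support that, because they give neither an any-of-nine rule nor a correlation, and higher correlations take the figure below 20%.

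A reader might also see a direct contradiction between the t tests under *Statistical analysis* and the relative risk under *Primary outcome*. That is too strong. The former section is generic and does not assign the t test to the primary outcome, and the relative risk fits the responder calculation. The real conflict is within *Sample size*, between its first and last paragraphs.

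Nor should the two-point reduction be read as 2 mm. The same section refers to a 10-point scale, so two points correspond to 20 mm on the 100 mm line. This is a unit inconsistency to tidy and no more.

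Finally, multiplicity methods are named. But Bonferroni and Benjamini-Hochberg appear as a test for medians in the section on secondary and safety outcomes. They do not protect the primary claim.

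None of this supplies a primary time point or chooses between the two definitions.

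**Conclusion.** The point holds: no single confirmatory test is fixed. This rests on the text alone and needs no assumption.

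The size is conditional. If a positive result at any of the nine times could be claimed on one definition, the false-positive risk would be about 37% with independence, about 20% at an assumed correlation of 0.7 and about 12% at 0.9, against a stated 5%. Even the lowest of these is more than twice nominal. Allowing both definitions adds to it, by an amount that depends on how they are modelled, so no single figure should be quoted for that case.

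It needs correcting before any unblinded analysis, because the choice of primary variable and time is credible only if it is made without sight of the results.

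**What to change.** - **Variable.** Name one: either the responder rate, with the event defined and analysed by relative risk, or the VAS score with a between-group comparison of means. The choice is the sponsor's.
- **Time.** Name one time point, or one summary over stated time points.
- **Test.** Name one test at two-sided 5%, and say that this level belongs to that test.
- **Sample size.** Keep only the matching calculation, in mm on the 100 mm scale (a 20 mm reduction, or a 10 mm difference), and correct the printed alpha of 0.5 if the score version stays. The SD must apply to the chosen time point or summary. The 1.6 has no stated time point and should not be carried over unchecked to, say, an average over several days.
- **The rest.** Make the other definition, all other time points and Dennis's pain scale secondary.

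**Cost.** This is a change of wording. The sponsor gives up claiming a primary result at the other time points or on the other definition. One consequence should be weighed when choosing: the responder calculation reaches 58 with no allowance for drop-out. If the stated 28% applied to it, 58 × 0.72 ≈ 42 per group would be evaluable, with power of about 66%, and keeping 58 evaluable would need 58 / 0.72 = 80.6, so 81 per group. The score version already includes the 28%.

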### Secondary outcomes

The EUROQOL-5 and Short-form health survey (SF-36) will be used as generic quality of life questionnaires. The Roland Morris disability questionnaire will be used as a specific outcome for low back pain, and the capacity to work will be evaluated according to Dennis’s work scale. The HADS (Hospital Anxiety Depression Scale) will be evaluated preoperatively and during follow-up.

### Radiographic images

The fracture will be evaluated on plain radiographs (AP and lateral) and CT preoperatively and after the surgical procedure. During follow-up (1, 2, 3, 6, 12 and 24 months), only plain radiographs (AP and lateral) will be used for evaluation.

On the plain radiographs, the AP alignment and deviation will be evaluated. On the lateral radiographs, the height of the fractured vertebral body, height of the vertebral body above and below the fractured vertebra, kyphosis of the injured vertebral segment, kyphosis of the fractured vertebra, implant breakage or loosening will be evaluated. On CT, the compression of the spinal canal, sagittal and coronal diameters of the spinal canal, lamina fracture and position of the screw inside the pedicle will be evaluated.

### Withdrawal of patients from the study

Patients will be withdrawn from the study if they meet any of the following criteria: (a) the patient chooses to be withdrawn from the study without giving a reason, following the terms in the Helsinki declaration; (b) the patient develops a disease or condition that might interfere with the study results, such as spinal tumor disconnection; or (c) the patient presents any problem related to the study or is non-compliant.

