## Methods/design

This will be a multi-center randomized controlled trial to assess the effect of minimally invasive percutaneous surgery versus conventional open surgery in patients with thoracolumbar spine fractures with an indication for posterior stabilization. The primary endpoint will be the postoperative pain, evaluated through the visual analogue scale (VAS) and compared between the patients subjected to minimally invasive percutaneous surgery and those subjected to conventional open surgery. The follow-up period will be two years, during which time the patients will fill out questionnaires and be evaluated both clinically and radiologically. Conventional open surgery and minimally invasive percutaneous surgery will be compared in patients with thoracolumbar spine fractures with indication for posterior stabilization. The study is designed as a multi-center (five centers) study. The follow-up period is 2 years, during which time the patients will fill out questionnaires and be evaluated both clinically and radiologically.

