### Randomization

Patients who meet the inclusion criteria and have provided informed consent will have their fractures classified according to the system proposed by Magerl et al. The randomization process will be performed for each fracture type (A, B and C). The patients will be randomly allocated into the following two groups: A- conventional open surgery and B- minimally invasive percutaneous surgery. The randomization will be performed via a centralized system. The research team will contact the central randomization system informing the type of fracture (A, B or C). The type of treatment will then be assigned by this system, with the patient being subsequently allocated to the appropriate group. We will use envelopes for each fracture type, following the CONSORT (Consolidated Standards of Reporting Trials) guidelines. The randomization will be performed using numbers generated by a specific software [MedCalc Statistical Software version 18.11.3] and will obey the 1:1 ratio for each group [MedCalc Software bvba, Ostend, Belgium; https://www.medcalc.org; 2019].”general anesthesia. Stability of the spine will be achieved by bilateral short-segment pedicle instrumentation. Pedicle screws will be inserted into the vertebral body one level above and below the fractured vertebra. The fractured vertebra will also be included in the fixation. In the fractured vertebra, a short pedicle screw will be inserted uni- or bilaterally according to the degree of pedicle involvement.

The spine fixation system is composed of a 6.5-mm-diameter polyaxial pedicle screw attached to 5.5 mm rods. The vertebral fixation system will be applied through the conventional open approach in group A (open approach) and percutaneously without open exposition of the injured vertebral segment in group B (minimally invasive percutaneous surgery). Posterior fusion using bone grafts or bone substitutes will not be performed in either group. External immobilization will not be used after surgery, and the patients will be allowed to walk according to their general clinical picture and pain.

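### Compulsory study withdrawal for an interfering condition, a study-related problem or non-compliance creates avoidable missing outcomes and undermines the stated intention-to-treat principle

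*Protocol article*

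**What the plan says.** The section 'Withdrawal of patients from the study' is worded as an obligation: "Patients will be withdrawn from the study if they meet any of the following criteria". There are three criteria. The first is the patient's own choice and raises no difficulty. The second, (b), applies when "the patient develops a disease or condition that might interfere with the study results". The third is "c) the patient presents any problem related to the study or is non-compliant". The article defines neither a study-related problem nor non-compliance.

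The 'Primary outcome' paragraph of the statistical section stresses that "in this clinical trial the intention-to-treat (ITT) principle will be used".

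The two groups are "A- conventional open surgery and B- minimally invasive percutaneous surgery". The primary outcome is VAS pain on the first three postoperative days and at 1, 2, 3, 6, 12 and 24 months ('Primary outcome measure'). Questionnaires and plain radiographs follow the same monthly schedule.

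Two other sections bear on the point. 'Informed consent and patient safety' says complications are treated and followed until they settle. 'Complications, adverse events, and additional surgery' says adverse events and complications are followed throughout the study and that related further operations are recorded. Neither mentions VAS, questionnaires or routine radiographs after a patient has been withdrawn.

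**The concern.** An intention-to-treat comparison needs outcomes from randomised patients whatever happens to them after randomisation. Criteria (b) and (c) make certain later events a reason to leave the study. Criterion (b) selects patients by their possible effect on the results. Criterion (c) is open enough to cover missed visits, departure from the assigned approach or a difficult recovery.

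Withdrawal rules are sometimes meant to protect a patient from further study treatment. Here the study intervention is a single operation, so afterwards there is little left to stop except measurement. If withdrawal is related to both arm and pain, the later VAS comparison rests on a selected subset. An analysis plan can state how missing values are handled, but it cannot recover scores that were never collected because the protocol ordered withdrawal.

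**Working it through.** **1. The two rules side by side**

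| Question | Withdrawal section | Statistical section, primary outcome |
|---|---|---|
| Who stays under observation? | Not patients meeting (b) or (c) | Not stated |
| Who is analysed, and in which arm? | Not stated | All as randomised, by the ITT principle |
| Are earlier data discarded? | Not stated | Not stated |
| Is VAS collected after withdrawal? | Not stated | Not stated |

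The two texts are not formally incompatible: a withdrawn patient can be analysed as randomised with later visits missing. The conflict is practical, because the first rule removes data that the second depends on.

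**2. Which outcomes are exposed**

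VAS on days 1 to 3 is taken soon after surgery and nothing says it is deleted. The visits from 1 to 24 months are most exposed. Adverse events, complications and reoperation have their own follow-up promise.

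**3. The plan's own figures**

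'Sample size' gives 58 per group for 50% against 25%, two-sided 5%, power 80%. The pooled two-proportion formula, with mean proportion 0.375, reproduces it:

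n = [1.96·√(2·0.375·0.625) + 0.84·√(0.5·0.5 + 0.25·0.75)]² / 0.25² = (1.342 + 0.556)² / 0.0625 ≈ 57.6, so 58.

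(The formula as printed, unpooled, gives 54.88, so 55. That is a separate matter and does not affect this point.)

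The anticipated drop-out is 28% from all causes: 58 × 0.72 = 41.8, about 42 left per group. Power for 50% against 25% is 80.2% with 58 and 66.3% with 42. For the section's other target, one point with SD 1.6, it is 92.0% and 81.7%. Avoidable withdrawals would add to, or form part of, that loss; the article does not say which.

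**4. Illustration of selective removal (assumed, not from the documents)**

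Suppose there is no true effect, the response probability is p in both arms, 58 are randomised per arm, and only non-responders are removed, equal to a fraction w of an arm. The observed rate in that arm becomes p / (1 − w).

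- Equal removal: both arms show p / (1 − w), so the difference is 0. With p = 0.25 and w = 0.14 in each, both show 29.1%.
- 0% against 10%, p = 0.25: 0.25 / 0.90 = 27.8%, a difference of 2.8 points.
- 0% against 10%, p = 0.50: 0.50 / 0.90 = 55.6%, a difference of 5.6 points.

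The type I error of a nominal 5% pooled z-test, with 58 and 58 × 0.90 = 52.2 patients, follows from difference / SE:

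- p = 0.25: 0.0278 / 0.0840 = 0.33, giving 6.3%.
- p = 0.50: 0.0556 / 0.0953 = 0.58, giving 9.0%.

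The sign depends on which arm loses the patients, and the documents do not indicate which.

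**The case against.** The strongest reply is that ITT governs who is analysed and in which arm, while the withdrawal section governs who stays in follow-up. That section does not exclude withdrawn patients from the analysis, discard their earlier data or replace them, and the handling of missing visits is commonly left to an analysis plan. This stands against any claim of outright contradiction. It does not rescue the rule, because stopping collection is an instruction the article itself gives.

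Four stronger readings are tempting and are not supported.

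- *Patients with complications are the ones removed, and complication follow-up stops.* The withdrawal section does not name complications, poor recovery or reoperation. Further surgery at the operated level is counted as a poor result, with one exception, so it is treated as an outcome. Complications are also promised follow-up elsewhere. At most, the scope of (c) against those sections is unclear.
- *Unblinded staff decide.* The article does not say who decides on withdrawal. Surgeons necessarily know the approach, but the masking of others is not described either way.
- *The 28% measures this problem.* It is drop-out from all causes. Assigning it all to non-responders in one arm and none to the other would give 9.7 to 19.4 points for true response of 25% to 50%, with type I error of 18% to 49%. Nothing in the article supports such a split.
- *Bias is certain.* It requires removal that differs by arm and is related to outcome. That is plausible but not shown.

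**Conclusion.** The point holds as a badly fixed conduct rule. Criteria (b) and (c) compel withdrawal from the study for undefined events after randomisation, no text continues the collection of VAS, questionnaires or routine radiographs, and the stated ITT principle is undermined, mainly for the 1 to 24 month visits. The reading of the text needs no numerical assumption.

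The size of any bias does rest on assumption. It ranges from none, if non-responders are removed equally and there is no true effect, to about 3 to 6 percentage points if non-responders equal to 10% of one arm and 0% of the other are removed. The documents fix neither the amount nor the direction. The change is still worth making, because uncollected outcomes cannot be restored at the analysis stage.

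**What to change.** Rewrite the withdrawal paragraph as follows.

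- Participation ends only when the patient withdraws consent; the existing right to leave at any time is kept.
- Criteria (b) and (c) are removed as grounds for ending follow-up. Such events are recorded, with date and reason.
- VAS, questionnaires and radiographs continue on the published schedule for every other randomised patient, and all patients are analysed in the arm assigned. Data collected before a withdrawal are kept.
- The paragraph is reconciled with 'Informed consent and patient safety' and 'Complications, adverse events, and additional surgery', so that an event counted there as an outcome cannot also serve as a reason for withdrawal.

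The cost is a one-paragraph amendment and some extra follow-up effort on patients who would otherwise be dropped. The visits are already scheduled, and no rule of clinical care changes.
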